#### **Description of Measures:**

**MRI data acquisition:** will be obtained using the same 3T MRI instrument using phased array RF coils housed in the OHSU/Advanced Imaging Research Center (AIRC). Subjects will undergo anatomical imaging sequences similar to those used in the ADNI. We will use the following protocol: 1) T1-weighted magnetization prepared rapid gradient echo (MPRAGE): TE = 3.4 ms; TR = 2300 ms, TI = 1200 ms; 1 mm isotropy; full brain coverage; FOV 256 mm; 2) T2/Proton density (PD) dual fast spin echo: TE = 11 ms, TR = 3,000 ms, slice thickness = 3 mm in-plane resolution 0.9 mm, 3) Fluid attenuated inversion recovery (FLAIR): sagittal, TE = 388 ms; TR = 6,000 ms, TI = 2,100 ms; 1 mm isotropy; full brain coverage; FOV = 250 mm, and 4) Diffusion tensor imaging (DTI): TR = 9500 ms; TE = 95 ms; slice thickness 2.0 mm; 30 directions. Total MRI acquisition time will be less than one hour. Imaging data will be stored in a secure server located in the AIRC at OHSU. In order to maintain scanner stability over time, ADNI quality assurance measures (i.e., calibration phantom and retrospective image correction) will be implemented, 4) Arterial spin labeling (ASL), 5) Hemorrhage sequence.

#### **MRI Data analysis:**

**Subject inclusion criteria:** Total WMH volume: For the purpose of enriching a study population with enhanced WMH burden, a preliminary determination of WMH severity will be assessed using FLAIR images. At the screen II visit, axial FLAIR MRI images will be quantified to determine high total WMH ( $\geq 5$  cc).

**MRI Primary Outcome:** Volumetric total WMH segmentation: Freesurfer tissue segmentation is performed on the T1 images. FLAIR images are affined registered to T1 sequences using FLIRT with 6 df and masked by WM tissue masks from Freesurfer. The mean and SD of intensities within the WM mask are calculated with AFNI tool (3dMaskAve). Clusters of voxels over 2.5 standard deviations above the mean in intensity are used as seed voxels for a cluster-growing algorithm^73. A customized matlab script calculates the mean signal intensity within each cluster and iteratively incorporates all nearest neighbor voxels that are within 5% signal intensity and within the WM mask. Approximate voxels with similar intensity are added to each cluster, the mean is recalculated, and the process repeats until surrounding voxels of similar intensity are absent. Clusters of contiguous WMH voxels, which extend to the border of the lateral ventricle, are automatically labeled periventricular while all other clusters are labeled deep. This WMH segmentation method is validated in house against WMH volumes obtained by manual tracings ( $R^2 = 0.92$ , plot not shown). The fully automated method produces excellent intra-rater (ICC = 0.99) and inter-rater (ICC = 0.99) reliability.

**MRI Secondary Outcomes:** 1) Voxel-Based Morphometry (VBM) analysis uses Statistical Parametric Mapping (SPM) software, normalized and segmented in Montreal Neurological Institute (MNI) stereotactic space is used to examine regional differences in grey matter volumes between the active and placebo groups 2) Volumetric Brain MRI will use Freesurfer to determine the group differences in medial temporal lobe volume changes, which is another region that may be sensitive to pufas. 3) DTI and TBSS will examine regional, between group differences in white matter tract integrity previously linked to pufa supplementation. Voxel wise statistical analysis of FA data is performed using TBSS and FSL. FA images are created by fitting a tensor model to the raw diffusion data using FSL's diffusion toolbox, and then brain-extracted. FA data is then aligned into a common space using the nonlinear registration tool FNIRT. Mean FA image is thinned to create a FA skeleton representing the center of all tracts common to the group. Each subject's aligned FA data is then projected onto this skeleton and the resulting data is fed into voxel wise cross-subject statistics. Mixed effects models determine time point, group and interaction effects. 4) ASL will examine cerebral blood flow.

**Biomarkers and Diet Survey.** Plasma fatty acids are measured using GC/MS, soluble adhesion molecules and inflammatory products (sICAM-1, sVCAM-1, E-Selectin, TNF $\alpha$ , IL-6, hsCRP), and beta amyloid metabolites (abeta 40 and 42) with ELISA, enzymatic methods for lipids, PCR for APOE4 in the OHSU/Oregon Clinical & Translational Research Institute's Core Laboratory. For plasma PUFA (EPA + DHA)  $< 5.5\%$  total fatty acids at screening visit 1, the Homan Omega 3 blood spot test will be used as this test allows for a 10 day turn-around of results, ensuring that we will meet all baseline inclusion/exclusion criteria in a timely fashion. These measures (except APOE4) are collected at baseline, 3, 6, 12, 18, 24, 30 and 36 months.

The Food Frequency Questionnaire is collected at baseline and at month 36 to assess stability of diet during the course of the study and assess any dietary drift within treatment groups.

### **Neuropsychological assessment (Admin total time ~ 45 minutes)**

*Trail Making Test. Trails A:* number sequence administered to familiarize participants with the task. *Trails B:* Investigates speed of attention, sequencing, mental flexibility, visual search and set shifting. Participants are asked to join 25 randomly displayed numbers and letters in an alternating and sequential fashion. [Admin 10 minutes]*Digit Symbol Test.* The WAIS-IV Digit Symbol Test is a visuographic-coding task in which participants code numbers into symbols using a key. Speed is scored. [Admin 3 mins]

*Category Fluency (Animals & Vegetables):* Subject is asked to name, as fast as they can, all of the things that belong in a given category. Subjects will be given 60 seconds to name items in the category of Animals, and an additional 60 seconds to name items in the category of Vegetables. [Admin. 5 mins]

*Letter Fluency (C & L):* Subject is asked to name, as fast as they can, all of the words they can think of that begin with certain letters. Subjects will be given 60 seconds to name words that begin with the letter “C,” and an additional 60 seconds to name items that begin with the letter “L.” [Admin. 5 mins]

*Multilingual Naming Test (MiNT):* Participants are shown a picture of an object, one at a time, then asked to name the object. Participants are scored for correct responses, as well as prescribed prompts. This test is designed to assess naming skills. [Admin. 5 mins]

*Craft Story 21 Recall:* This test assesses memory. Participants are asked to repeat back a short story. Participants are scored on verbatim responses and separately on paraphrased responses. Participants are asked to recall this story again after a 20 minute delay. [Admin. 10 mins]

*Number Span Forward & Backward:* This test assesses attention and short-term memory. Participants hear a list of numbers and must repeat them in the same order. Participants will also hear a separate list of numbers and be asked to recount them in reverse order. [Admin. 10 min.]

*Benson Complex Figure Copy:* This task assesses memory and visuospatial processing. Participants view a complex design and are asked to replicate it, and then do so again after a 15 minute delay. [Admin. 10 mins]

Order of administration: WAIS-IV Coding, MoCA, Craft Story 21 Immediate Recall, Benson Complex Figure Copy Immediate Recall, Number Span Forward, Number Span Backward, Category Fluency (Animals & Vegetables), Trail Making Test A, Trail Making Test B, Craft Story 21 Delayed Recall, Benson Complex Figure Copy Delayed Recall, MiNT, Letter Fluency (L & C).

### **Global cognitive, functional, mood and gait speed assessments:**

*Clinical Dementia Rating (CDR):* measures dementia severity and is a global rating of dementia with scores ranging from 0 to 3 (0, 0.5, 1, 2, and 3) rated by a semi-structured subject and informant interview. A clinician synthesizes the cognitive and functional abilities based on 6 domains, including memory, orientation, judgment and problem solving, community affairs, home and hobbies, and personal care. The scale has good inter-rater agreement. Participants with a CDR score < 1.0 will be eligible and confirmed clinically as non-demented.

*MMSE:* The Folstein MMSE is a 30-point scale is a global cognitive measure collected to facilitate comparison across studies and used to determine eligibility. Potential participants with MMSE >23 will be eligible.

*Montreal Cognitive Assessment (MoCA):* A rapid screening instrument for assessing different cognitive domains. Subjects are asked to do the following tasks: 1.) Join 10 randomly displayed numbers and letters in an alternating and sequential fashion. 2.) To measure visuoconstructional skills, accurately copy two drawings, a cube and a clock. 3.) Provide the names of three animals represented by drawings. 4.) Remember a list of 5 words. This is repeated 2 times. After a delay, subjects again recall as many words as possible. 5.) To

measure attention: repeat a five number sequence forward, and a separate three number sequence backwards, signal when a certain letter is read in a spoken sequence of varying letters, and count backwards from 100 by subtracting seven. 6.) Name as many words that start with the letter “F” in sixty seconds. 7.) Explain what pairs of words have in common, such as “Tell me how an orange and a banana are alike.” 8.) To provide orientation, provide date, place, and city. [Admin. 10 min.]

*Geriatric Depression Scale-15.* The GDS-15 is a widely used instrument for screening depression in the elderly. It is brief, non-somatically focused, and can be either observer or self-administered. The scores range from 0 to 15, with higher scores indicating more severe depression. The GDS-15 was developed and originally validated in elderly patients. [Admin 5 mins]

*Instrumental Activities of Daily Living:* Measures an individual’s ability to carry out tasks that are important for daily living. The IADLs are collected to capture functional changes [Admin 10 minutes]

*Timed Gait Test:* WMH is associated with slowed gait speed. A 10-yard (30 foot) course will be measured and marked on a straight unobstructed area prior to test administration. Participants will be instructed to walk the 10 yards as quickly as possible without running, cross a line, turn around, and walk back the 10 yards. The average time of three trials is recorded in seconds.

#### Central (Aortic) Blood Pressure

CardioScope TM is a non-invasive, compact standalone measurement device that automatically measures systolic and diastolic pressure, and pulse rate in adult and pediatric patients.

CardioScope also provides non-invasive central (aortic) systolic, mean and diastolic blood pressure, and pulse waveform intended for use in adult patients. The CardioScope first measures brachial systolic and diastolic blood pressures and pulse rate using the Oscillometric method. It then inflates the cuff to a pressure about 30 mmHg higher than systolic (Suprasystolic) pressure to acquire a further oscillometric pulse waveform. The suprasystolic pulse waveform is used in combination with the conventional upper-arm blood pressures to derive central systolic, diastolic and mean blood pressures. Central blood pressure will be taken at Screen II (visit 2), and months 12, 24, and 36.

**Safety labs.** Will include a CBC, CMP and PT/INR. These labs are assessed at screen, 6, 12, 18, 24, and 36 months.

| Year                          |  | 1                | 2                | 3              | 4              | 5                     |
|-------------------------------|--|------------------|------------------|----------------|----------------|-----------------------|
| IRB approval           |  | X                |                  |                |                |                       |
| Enrollment at Baseline |  | N=75             | N=150            | Attrition n=15 | Attrition n=14 | Attrition n=11, n=110 |
| Intervention           |  | X                | X                | X              | X              | X                     |
| Data collection        |  | X                | X                | X              | X              | X                     |
| Data Analysis          |  | Enrollment stats | Enrollment stats | Baseline stats |                | Primary outcomes      |

## E. HUMAN SUBJECTS

### 1. Risks To Human Subjects

#### 1.A. Human subjects involvement, Characteristics and Design

A total of 150 participants age 75 and older will be enrolled, and randomized to assigned treatment group after meeting screening criteria; will be followed over three years. Participants will be recruited from Oregon Health & Science University, Portland, OR and the surrounding communities including Vancouver, Washington. Participants will non-demented and have a CDR of  $\leq 0.5$ , and screening will include a MRI and blood test to enrich the population with white matter lesions and relatively lower plasma pufas. The Inclusion/Exclusion criteria are described under Approach, Study Population. We will recruit approximately equal numbers of men and women, and no ethnic group will be excluded. Because of the demographics in the state of Oregon we do expect to recruit a larger number of white non-Hispanic than might be reflected across the U.S. Eighty-seven percent of all Oregonians are white with about 10% combined being Black, Asian or Pacific Islander, or Hispanic. Study inclusion requires all study participants have a partner that spends at least 1 hour/day or 1 day per week with the participant to corroborate independence of activities of daily living. Non-demented

persons of advanced age are particularly vulnerable to brain health changes, which are insidious in younger populations. Enriching our study population by advanced age, white matter disease and low pufas status is necessary to assure higher power to test our hypothesis that pufas slow white matter disease and the associated cognitive consequences of its progression. Allocation of study supplement assignment is double blinded and randomized 50:50. The intervention is chosen on the basis of our first-hand experience and proven safety and efficacy in raising the key pufas to a predictable tissue level.

### **1.B. Sources of materials**

Study measures will be collected from participants ten times over the 36-month intervention (screen/baseline, 3, 6, 12, 18, 24, 30, and 36-months). Study measures include brain MRI, Cognitive, Global, Functional and Behavioral assessments, blood and DNA. Outcomes include, MRI, Cognitive (attention and processing speed, working memory, executive function, memory, language, visuospatial skills and global cognition), Functional (ADLs, gait speed), blood pressure,, blood-based biomarkers of endothelial function and lipid metabolism collected at baseline, 3 and 6 months, and then every 6 months over 3 years. Central aortic blood pressure will be collected at Screening Visit II, and then once every year. Safety lab work (CBC, CMP, and PT/INR. Data from safety labs measured at screening, 6, 12, 18, 24 and 36 months will be processed and reviewed for safety. Medical record reports, including labs and MRI report along with PE/neurological exam, will be used to help with inclusion/exclusion criteria on the screening visits. Once the treatment intervention begins subject AE will be collected in “real time” and discussed during weekly team meeting. Data for compliance by pill count will be collected every 3 months. Drs. [name] (statistician), [name] (site PI), and [name] (grant PI) along with the [name], informatics core of OHSU’s NeuroNext will facilitate data collection, management and protection. [name] will perform the data analysis. All data sources will have a unique ID number that has no personal identifiable information to support confidentiality. All study files will be stored in locked file cabinets and keys provided under the supervision of the [name] (site PI) for appropriate staff (e.g. study coordinator, research assistant). All data obtained from this study will be used for research purposes only and will comply with HIPAA regulations.

### **1.C. Potential Risks**

Venipuncture: The risks are minimal and may include some pain, bleeding and transient hematomas.

Questionnaires: The risk from filling out diet habit questionnaires and psychometric tests are minimal, there may be mild anxiety from filling out questionnaires.

Omega-3 pufas and soybean oil placebo: At the daily dose given in this study, 1650 mg of omega 3 pufas (975 mg EPA + 675 mg DHA), the risks are minimal. This dose is Generally Regarded As Safe (GRAS) by the FDA. Potential side effects include fishy belches, and mild gastrointestinal effects (nausea, loose stools, indigestion). Because fish oil does have anti-platelet and anti-thromboxane A2 effects there is a concern about increased bleeding time and interactions with blood thinning medications (e.g. warfarin). Although a study evaluating the effects of 1-year of fish oil supplementation on patients undergoing artery bypass reported no increase in bleeding during surgery in patients given fish oil plus aspirin or given fish oil plus warfarin compared to patients given those therapies alone. This study will monitor bleeding time by PT/INR as a protection against this risk. Soybean oil will be given at 3 grams per day, like the omega 3 pufa; the risks are minimal and may include mild gastrointestinal effects.

As a protection against any risk, adverse event reports will be monitored every 3 months either by phone or in-clinic and participants. A CBC, comprehensive metabolic panel will be collected at screening, 6, 12, 18, 24 and 36 months to monitor any treatment effects on organ function as another protection against risk.

MRI: Risk to having a brain MRI is minimal. Feeling claustrophobic is a risk. We are excluding subjects with MRI contraindication (i.e. pacemakers, cranial plates) to minimize risks.

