**Adverse events.** Adverse events will be monitored in “real time” with weekly review of AE’s with study staff using clinical judgment to determine reporting to IRB and FDA. An external data safety monitoring board (DSMB) will convene biannually to study unblinded data on AE coded by organ system. Although assessment of AEs will also include solicitation of non-specific change (e.g., “do you feel different since beginning the treatment?”), a 12-item AE checklist covering all major organ systems will be included to probe for AEs. The nature of each AE, its severity (mild, moderate, or severe), its likely relationship to study treatment (definite, probable, possible, not related, or unknown), its duration, and any necessary treatment modifications or adjustments will be recorded. In addition to the monitoring and recording of AEs at each 3 month subject contact, labs to assess basic metabolic function (including liver function tests), CBC and PT/INR are performed at screening and at months 6, 12, 18, 24 and 36. Incident use of oral anticoagulant therapy is identified through subject interview that occurs every 3 months. Incident anticoagulation therapy cases are asked to stop the supplement and complete complete the remaining follow up visits. Participants will be reminded and encouraged during clinic visits and phone checks to contact the study coordinator or investigator if a moderate or serious AE occurs.

**Compliance:** Compliance will be measured in-clinic by pill count. In addition to the in-clinic checks on compliance, each subject will receive a phone call to check on compliance every 3 months. If a subject’s compliance drops < 80% at any time, they will be contacted by the trial coordinator by phone to find out why

and to aid the subject in finding ways to increase compliance. Although plasma fatty acid measurement is an independent measure of compliance, knowing the results of fatty acids levels during the study would un-blind the study. Plasma PUFA index will be used during data analysis to corroborate pill count.

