## **2.B. Protection Against Risk**

All information about subjects will be locked so that only authorized study staff will have access. Research records will be coded with a unique patient identification number; therefore will contain no personal identifiers. All records with identifying information will be locked so that only authorized study staff will have access to them. Data will be kept in locked cabinets separate from identifiers. Computer files will be password protected. No one other than the researchers will have access to identifiable data. Participants will be told that they have the right to refuse to answer any question(s). If they are upset by a question they will be referred to the Principal Investigator. We will monitor adverse events by laboratory tests, which include prothrombin time (PT/INR), CBC and CMP and by every 3-month adverse events report. We are monitoring the effects of treatment on CBC and CMP at baseline, 3, 6, 12, 18, 24 and 36-months. Subjects whose labs reflect significant abnormalities, at 3 months (that have not reported adverse events) will be further screened to determine the potential cause(s) of the lab abnormalities; if the study treatments are suspected, we will discontinue treatment and remove the subject from the study. A data safety monitoring board (DSMB) will convene biannually to study unblinded data on AE coded by organ system. All subjects will be given a telephone number and be instructed to call [name] or the trial coordinator if they believe they are experiencing severe side effects from the study medication.

Plan for informing participants and their caretakers of incidental findings with potential significance from MRI: The MRI derived from this study will be reviewed for clinically relevant findings that would impact health (i.e., cortical stroke, tumor, normal pressure hydrocephalus). If clinically relevant findings are identified, [name] or [name] will contact a neuroradiologist for a clinical read within 78 hours of identified finding.. The PI or study coordinator will notify the subject by phone within one week of the discovery to discuss the abnormal finding. The subject's PCP will be notified of the finding and the clinical brain scan will be provided to support subject the appropriate care.. [name] (sitePI) will also work with the PCP to facilitate an expedited referral to a specialist (e.g., neurologist, neuroradiologist) if the PCP deems necessary.

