## 5. Data And Safety Monitoring Plan

Adverse events will be monitored in “real time” with weekly review of AEs with study staff using clinical judgment to determine reporting to IRB and FDA. A data safety monitoring board (DSMB) will convene biannually to study unblinded data on AE coded by organ system. Although assessment of AEs will also include solicitation of non-specific change (e.g., “do you feel different since beginning the treatment?”), a 12-item AE checklist covering all major organ systems will be included to probe for AEs. The nature of each AE, its severity (mild, moderate, or severe), its likely relationship to study treatment (definite, probable, possible, not related, or unknown), its duration, and any necessary treatment modifications or adjustments will be recorded. In addition to the monitoring and recording of AEs, labs to assess basic metabolic function (including liver function tests), CBC and prothrombin time will be performed at screening and months 6, 12, 18, 24 and 36. Participants will be reminded and encouraged during clinic visits and phone checks to contact the study coordinator or investigator if a moderate or serious AE occurs.

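### Potential Risks says PT/INR monitors bleeding time, but PT/INR is prothrombin time and measures neither bleeding time nor the anti-platelet effect it is meant to guard against

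*Protocol*

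**What the plan says.** Section 1.C (Potential Risks) rates the risks of the supplement at the trial's dose as minimal. It singles out one mechanism, noting that "fish oil does have anti-platelet and anti-thromboxane" effects, and draws two worries from it: longer bleeding time, and interaction with blood thinners such as warfarin. It cites a bypass-surgery study that found no extra surgical bleeding when fish oil was added to aspirin or to warfarin. It then states the protection: "This study will monitor bleeding time by PT/INR as a protection against this risk".

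The same test is described differently elsewhere:

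- Section 2.B (Protection Against Risk): "We will monitor adverse events by laboratory tests, which include prothrombin time (PT/INR), CBC and CMP and by every 3-month adverse events report".
- Section 5 (Data And Safety Monitoring Plan): "CBC and prothrombin time will be performed at screening and months 6, 12, 18, 24 and 36".

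The safety panel is CBC, CMP and PT/INR in Table 7 (footnote 3) and in the Safety labs paragraph.

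General safety capture is described in the Adverse events paragraph and in section 5. There is open questioning at each 3-month contact, and "a 12-item AE checklist covering all major organ systems will be included to probe for AEs". The DSMB "will convene biannually to study unblinded data on AE coded by organ system".

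Exclusion criterion 14g lists anticoagulants (vitamin K antagonists, factor Xa inhibitors and others, low molecular weight heparins). Participants who start one during the trial are asked to stop the supplement and stay in follow-up.

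**The concern.** The section that explains how participants are protected pairs a named biological effect with a named test, and the test does not measure that effect. The mechanism given is on platelets, and the quantity said to be monitored is bleeding time. Prothrombin time is neither a platelet measure nor a bleeding-time measure.

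What is at stake is how the safety evidence is read. The protocol says the study will test the safety of the supplement (section 4, Importance Of Knowledge To Be Gained). Anyone taking section 1.C at its word (an ethics committee, the DSMB, or a reader of the final report) could take an unremarkable PT/INR table as showing that the anti-platelet concern had been watched and had not materialised. The table could not show that.

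**Working it through.** There is no rate, power or sample size to recompute. The check sets the statements side by side.

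1. **Which test is it?** Section 1.C calls what PT/INR measures bleeding time. Sections 2.B and 5 call the same test prothrombin time. These are different quantities, so the protocol gives two incompatible descriptions of one assay.

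2. **Does the test match the effect?** The effect named in 1.C is anti-platelet and anti-thromboxane. As a matter of general laboratory knowledge, prothrombin time reflects clotting-factor function. It can stay normal while platelet function is reduced.

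3. **Does another scheduled lab fill the gap?** The panel is CBC, CMP and PT/INR, drawn at screening and at months 6, 12, 18, 24 and 36, which is five on-treatment draws. A CBC normally gives a platelet count and may reflect blood loss, but it does not measure platelet function. The Table 7 biomarkers are fatty acids, endothelial and inflammatory markers, amyloid metabolites and lipid fractions. No bleeding-time or platelet-function measurement is listed.

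4. **Does the warfarin half of the concern rescue the sentence?** PT/INR is relevant to a warfarin interaction. However, anticoagulant users are excluded at entry, and those who start one are asked to stop the supplement. New use is found by interview every 3 months, so what PT/INR could usefully track is mostly the short interval before that interview. The part of the risk that PT/INR suits is largely designed out.

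5. **Is the platelet half also designed out?** No. The exclusion list names anticoagulants but no anti-platelet drugs, and the cited bypass study shows that use of fish oil with aspirin was in mind. Participants are 75 or older and selected for vascular burden on MRI.

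6. **What can still detect clinical bleeding?**
   - Adverse event contacts every 3 months: 36 / 3 = 12 contacts per participant, matching the 12 marks in Table 7.
   - CBC at the five on-treatment draws.
   - Physical and neurological examination at months 6, 12, 18, 24, 30 and 36.
   - MRI at screening and at months 12, 24 and 36, with review for clinically relevant findings. A hemorrhage sequence is listed under MRI data acquisition, although no text assigns it to safety monitoring.
   - Weekly staff review of adverse events and twice-yearly unblinded DSMB review.

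Steps 1 to 5 show that the dedicated protection does not measure what it is said to measure. Step 6 shows that this is a fault in the stated protection, not an absence of safety surveillance.

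**The case against.** The strongest reply is that this is one badly worded sentence in an otherwise layered safety plan. The protocol calls the risks minimal. The stated risk has two parts, and PT/INR is relevant to the interaction part. Bleeding would be recorded as an adverse event whatever the PT/INR showed, and no section says that the safety conclusion will rest on PT/INR. How adverse event terms are pooled and tabulated is usually left to the SAP or the DSMB's own documents, so the absence of a bleeding category in the protocol is not a fault in itself.

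Most of this stands, and it limits the point. It does not remove it, because the finding is about what the protocol states, not what it omits. It assigns a specific test to a specific effect, and the assignment is wrong. The interaction argument helps little once anticoagulant users are excluded and new users stop the supplement.

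A reader might infer more than the documents support:

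- *That bleeding would go undetected.* Not supported: the routes in step 6 of the working remain open.
- *That bleeding is the one serious hazard of the trial.* The protocol never calls it serious. It only gives it a dedicated protection.
- *That coding by organ system would scatter bleeds over several rows and hide an imbalance.* This is possible, but the 12 checklist items, the coding scheme and the DSMB tables are not shown. A bleeding or haematological item may already exist.
- *That the pilot bounds the bleeding risk.* Table 6 of the protocol has no bleeding row. It does not report zero bleeds, so no upper bound can be taken from it.

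**Conclusion.** The statement that PT/INR monitors bleeding time is wrong as written and conflicts with sections 2.B and 5. PT/INR results cannot serve as evidence that the anti-platelet effect named in section 1.C was monitored, and no other scheduled lab can take their place.

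The defect has no numerical size. It affects one safety claim and how the PT/INR data may be interpreted. It does not touch the primary outcome, the power calculation or the efficacy analysis, and it does not show that bleeding events would be missed. It is worth correcting because the claim sits in the participant-protection section and the remedy is cheap.

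The conclusion rests on two items of general laboratory knowledge that the protocol does not spell out: prothrombin time is a clotting-factor test, and a CBC does not assess platelet function. It also takes the lab panel listed in Table 7 and the Safety labs paragraph as complete.

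**What to change.** 1. In section 1.C, delete the statement that PT/INR monitors bleeding time and describe the test as in sections 2.B and 5: prothrombin time, kept as a general coagulation lab on its present schedule.
2. In the same place, state that the named effect is assessed through bleeding adverse events already collected at the 3-month contacts. These are pooled across organ systems into one prespecified category.
3. Show that category by arm to the DSMB at its twice-yearly meetings, with recorded anti-platelet or aspirin use as a descriptive split. Concomitant medications are already recorded at each contact. The term list and table layout can go in the SAP or the DSMB documents.

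The cost is a wording change in one section and one extra safety table. No new procedure or visit is needed, and no laboratory test, dose, eligibility criterion or stopping rule is proposed.
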